### Fidelity

The *PACT Online* edX course is static and hence remains the same for each participant who accesses it. For the telehealth consultations, all therapists will follow a consultation manual and will obtain clinical supervision from [name], [name] and [name] to ensure fidelity. [name] will also be the therapist for some families in the study. Records of intervention delivery and online course access will be kept, and telehealth sessions will be recorded.

### Control group: CAU

Families randomised to the CAU (waitlist control) group will receive their usual services (eg, medical, allied health, therapy) during the study participation period and will be offered the *PACT Online* intervention after completing the T3 follow-up assessment (at 6 months postbaseline). We will collect information on which services each family accessed throughout the study.

### Adverse events

Any adverse events will be recorded and reported in accordance with ethical procedures. The trial will be audited every 6 months from the beginning of recruitment by a clinical trials monitor indepedent of the study team.

### Patient and public involvement

*PACT Online* was developed grounded in parent feedback collected through our qualitative research,^16^ during which parents told us they wanted a parenting support intervention that was flexible and specific to their needs as parents of children with NDD. The intervention was refined grounded in further qualitative feedback from participants in the first PACT trial.^24^ From the outset, the current project has included a consumer representative (FR), who has also established a consumer engagement panel, which will be maintained throughout the project. The role of the consumer engagement panel involves providing feedback on intervention materials, assessments and assessment burden, and all participant-facing study documents (eg, information and consent forms, recruitment materials). In addition, the consumer engagement panel will be consulted on public dissemination of the study results, including the implementation recommendations.

This project also includes partner organisations including primary care (Paeds in a Pod), community-based allied health (BUSHKids; AEIOU Foundation for Children with Autism) and parent support organisations (NOFASD Australia, CP Alliance). All partner organisations have been involved in the study from the outset and have/will input into study design and documents, recruitment, dissemination of study results and the translation of outcomes into clinical practice. All partner organisations will be offered access to and training in *PACT Online* at the conclusion of the study. This training will be grounded in the implementation analysis.

### Outcome measurement

All assessments will be conducted remotely and/or online using REDCap for questionnaires and Zoom videoconferencing for collection of the EAS observational assessment footage and will be stored on REDCap and/or University of Queensland (UQ) servers with state-of-the-art data security meeting the requirements of the National Health and Medical Research Council and the Australian Code for Responsive Conduct of Research and accessible to study personnel only. Data will be destroyed after 15 years in accordance with UQ policy. In families with two participating parents, families will be encouraged to nominate the primary caregiver as the primary participating parent where applicable. The primary participating parent will complete all assessments at all time points. The secondary participating parent will complete a shorter online questionnaire (including measures of emotional availability, parental mindfulness, parent mental health, psychological flexibility, adjustment to child’s disability and health behaviour as well as economic evaluation measures) to minimise family burden. The questionnaires take approximately 1 hour to complete in total. The limitations of self-report measures are acknowledged.

### Baseline characteristics

*Demographic information* including family characteristics (eg, parent level of education, number of children), child diagnoses and perinatal risk factors (eg, alcohol consumption assessed using the AUDIT-C, pregnancy/birth complications) will be collected via questionnaire.

*The Gross Motor Function Classification System* is a parent-rated measure using a five-level system to classify children by age-specific gross motor ability, with published evidence of reliability and validity.^36^ It will be used to classify the functional abilities of all children with a physical disability.

### Primary outcome

#### Emotional availability

*EAS* measures the quality of the parent–child relationship across six scales: parental sensitivity, parental structuring, parental non-intrusiveness, parental non-hostility, child responsiveness and child involvement^15^ and a global relationship quality score. A 20 min naturalistic observation of parent–child interaction in the home will be recorded via Zoom and subsequently coded by experienced and accredited EAS coders, kept blind to the intervention condition and timepoint. Parents will be advised that during the recording, they should interact with their child in an ordinary, everyday way. For example, they could choose to play with toys, read a book, draw or perform any other interactive activity. Any child behaviour should be dealt with as they normally would. Extensive use of the EAS has demonstrated the excellent construct validity of this scale in establishing the expected relationship between EA and parent–child attachment, including in naturalistic observations in home settings.^15 37^ The EAS is appropriate for the full range of child ages in this study (0–10 years) with specific manuals guiding how to apply the same constructs for early (0–5 years) and middle (6–17 years) childhood. Our research group has achieved fair to excellent inter-rater reliability access the six scales in a similar study: parental sensitivity (ICC=0.72), parental structuring (ICC=0.51), parental non-intrusiveness (ICC=0.69), parental non-hostility (ICC=0.82), child responsiveness (ICC=0.82) and child involvement (ICC=0.71).

### Secondary outcomes

*EA-SR* (*36 items*) uses parent-report to measure emotional availability within the parent–child relationship.^27^ The EA-SR produces five subscales: mutual attunement, affect quality, capacity to involve the parent, intrusiveness and hostility. Responses are given on a 5-point scale ranging from 0=*not at all agree* to 4=*totally agree,* with a mid-point of 2 being *Neutral*. Good reliability estimates for the subscales have been found ranging from 0.71 to 0.84, with the exception of the affect quality subscale (α=0.49),^27^ which will be excluded from analysis if sufficient reliability is not achieved. The EA-SR has excellent validity and has been validated against the EAS.

#### Parental mindfulness

*The 10-item Interpersonal Mindfulness in Parenting (IM-P*) *Scale* assesses a parent’s ability to maintain present-centred attention and emotional awareness during parent–child interactions.^38^ The IM-P produces four subscales: present-centred attention, present-centred emotional awareness, non-reactivity/low-reactivity and non-judgmental acceptance. The IM-P has acceptable reliability (α=0.72) and strong support for its concurrent and discriminant validity has been obtained.^38^

#### Parent mental health

*The Depression Anxiety Stress Scales (DASS-21; 21 items*) assess symptoms of depression, anxiety and stress in adults.^39^ It comprises three scales, each with good internal consistency: the depression (α=0.91), anxiety (α=0.84) and stress (α=0.90) scales, and has good discriminant and concurrent validity when assessed against other validated depression and anxiety measures.^40^

#### Parent psychological flexibility

*Comprehensive Assessment of Acceptance and Commitment Therapy Processes (Com-PACT; 23 items*) measures psychological flexibility as core processes: openness to experience, behavioural awareness and valued action.^41^ It has good internal consistency (α=0.87–0.90) and good construct and convergent validity against psychological flexibility and distress measures (eg, a correlation of *r*=0.65 was obtained between the Com-PACT and the depression subscale of the DASS-21).^41^

#### Parent adjustment to child’s disability

*Parent Experience of Child Illness Scale (25 items*) assesses parental adjustment to a child’s chronic illness. An adapted disability-specific version will be used.^42^ It produces four domain scores: emotional resources, long-term uncertainty, guilt and worry, and unresolved anger and sorrow. It has acceptable reliability (α=0.72–0.89) and construct validity.

#### Parent health behaviour

*Good Health Practices Scale (16 items*) measures health behaviour in adults and has been validated in community samples, including by correlating with physiological biomarkers of poor health.^43^ It is summed to create a total score of 80, with higher scores indicating better health practices.

#### Parents’ goals for change

*Goal Attainment Scale (GAS)* will be used to identify three goals for change: (1) parent–child relationship or parenting goal, (2) parental self-care or health behaviour goal and (3) child behaviour/adjustment goal. Parents will use structured monitoring sheets to track frequency and/or duration of target behaviours, with final scores ranging from 0% (no improvement) to 100% (total success/goal attained). GAS has convergent validity against observational and parent-report measures and can be used to assess change across different types of behaviours.

#### Parent and child regulatory abilities

*Heart rate variability (HRV)*: changes in parent and child self-regulatory abilities will be assessed via HRV, an important physiological index of self-regulation,^44^ with higher HRV (ie, greater variability of the inter-beat intervals) related to better cognitive and mental health outcomes. HRV data will be collected using the Polar H10.

#### Child mental health

*Child Behaviour Checklist (CBCL parent report; 113 items*) assesses child behavioural and emotional problems: affective problems, attention deficit/hyperactivity, anxiety, oppositional defiance, somatic problems and conduct problems.^45^ The CBCL is well validated and appropriate for younger (1.5–5 years old) and older (6–18 years old) children, with age-specific versions.^45^

#### Child adaptive behaviour

*Vineland Adaptive Behaviour Scale Comprehensive (third edition VABS-III parent report*) is a measure of adaptive behaviour from birth to adulthood.^46^ Standard scores range from 20 to 160 for the four domains of communication, daily living skills, socialisation and motor skills, and an overall Adaptive Behaviour Composite. It has good internal consistency, test–retest reliability, inter-interviewer reliability and validity.^46^

### Implementation factors

#### Health economic evaluation

***Caregiver burden.** Carer Experience Scale (CES*) will be employed as a measure of caregiver burden. This validated measure of care-related quality of life has six domains (activities, support, assistance, fulfilment, control and relationship with the care recipient).^47^ The CES is scored from an algorithm based on norms in the general population and will be used to assess carer outcomes in economic evaluation.

**Health services utilisation**. The *Health Resource Use* questionnaire has been custom-built for the current research and will be used to collect healthcare utilisation information starting from baseline and for the duration of the study follow-up period. This questionnaire includes questions relating to the use of allied health services for children (eg, frequency, duration and cost of health services such as physiotherapy and paediatricians), mental health support for parents (eg, use and costs associated with mental health services such as psychologists and general practitioners) and parents’ satisfaction with the healthcare services they are currently accessing for both themselves and their child.

**Productivity loss**. Health and Work Performance Questionnaire (HPQ) will be used to measure parents’ productivity loss,^48^ a time cost calculated through absenteeism (ie, parent missed time from work) and presenteeism (ie, parent at work but less productive than usual and compared with others). The WHO HPQ has been widely used to assess absenteeism and presenteeism behaviours of workers. The HPQ has been found to have good reliability and validity as well as being sufficiently sensitive to change over time.^49^

**Health-related quality of life**. Parent health-related quality of life will be measured through the EuroQol five-dimension five-levels (EQ-5D-5L) questionnaire.^50^ The EQ-5D-5L questionnaire is a widely used preference-based generic scale that describes and assesses an individual’s health state across five dimensions: mobility, self-care, usual activities, pain/discomfort and anxiety/depression. Each is assessed through a five-level scale (no, slight, moderate, severe or extreme problems), with the uppermost level, indicating the greatest level of severity. Responses to the questionnaire are used to form a single utility score (EQ-5D-5L tariff) ranging from negative (less than zero) to 1.0 (full health) as an indicator of health status. A higher EQ-5D-5L utility score implies better health status.

#### Acceptability, appropriateness and feasibility

Questions assessing acceptability, appropriateness and feasibility are built into the *PACT Online* edX platform. Participants will be asked to rate each module in terms of usefulness on a 10-point Likert scale. In addition, they will have the opportunity to give written feedback in terms of usefulness, ideas for improvement and inclusivity.

#### Qualitative analysis of contextual factors for implementation

A purposive sample of parents in the *PACT Online* group will participate in semistructured interviews with two independent researchers (RO and NC) not involved in project management or intervention delivery. To gain in-depth insight into factors shaping implementation acceptability, interviews were selected to support a CFIR qualitative study design,^28^ prioritising individuals’ experiences of the intervention, settings and processes. Purposive sampling criteria (eg, age of child, carer relationship) will be defined iteratively after the first 10 interviews. Based on the ‘information power’ required,^51^ it is anticipated that recruitment will conclude after 30–40 inerviews. Grounded in CFIR,^28^ the interview guide prioritises discussion of acceptability, appropriateness and feasibility of implementing the intervention with parents as well as identifying contextual factors that act as facilitators and barriers to implementation success within the individual, inner setting and outer setting domains (see online supplemental materials for interview guide). The same independent researchers will also conduct qualitative interviews with the therapists delivering PACT Online and with some stakeholders from partner organisations as well as review a randomly selected subset of clinician notes.

### Statistical analysis of primary and secondary outcomes

The primary outcome will be analysed using mixed-model repeated-measures linear regression (multilevel modelling) with time (T1, T2, T3) and group (*PACT Online*/CAU) included as the main effects, and a time-by-group interaction term. Child will be included as a random effect to account for the repeated measures from each participant. Secondary comparisons will be conducted using linear models for continuous outcomes, logistic regression models for binary outcomes and Poisson models for count outcomes. The value of the outcome variable at baseline will be included as a covariate when appropriate. When repeated measures are analysed, the non-independence of results from the same family will be accounted for using mixed-effects models. Subgroup analyses will compare outcomes by child age and child diagnosis. Analysis will follow standard principles for RCTs with two-group comparisons using the intention-to-treat principle. In the event that >10% of outcomes are missing, we will conduct a sensitivity analysis to investigate the sensitivity of results. The pattern of missingness will be examined, and if the data are ‘missing at random’, we will use multiple imputation by chained equations, whereas if the data are determined to be ‘missing not at random’, we will use pattern mixture models.

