### Hypotheses

We hypothesise that families allocated to the *PACT Online* group, compared with families in the CAU group, will show improved emotional availability on the observational measure of the Emotional Availability Scale (EAS;^15^ immediately postintervention (T2; 12 weeks postbaseline, primary outcome). Furthermore, we predict that this effect will be sustained at follow-up (T3; 6 months post-baseline).

We hypothesise that families in the *PACT Online* group, in comparison to CAU, will show improved parent-reported emotional availability on the Emotional Availability–Self-Report (EA-SR;^27^ as well as improved parent outcomes across measures of (1) parental mindfulness, (2) parent mental health, (3) psychological flexibility (4) adjustment to child’s disability, (5) health behaviour and (6) regulatory abilities and improved child outcomes across measures of (1) mental health, (2) adaptive behaviour and (3) regulatory abilities at T2 (12-week postbaseline) and T3 (6-month postbaseline).

To describe and understand the context for implementation, we will consider the costs and consequences as well as the contextual factors that may influence implementation. Analysis of contextual factors will be guided by the consolidated framework for implementation research (CFIR)^28^ and will consider feasibility, acceptability and appropriateness of PACT Online, sustainability potential and contextual factors that could impact on implementation success.

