### Sample size

The sample size calculation is based on the between-group difference for the primary outcome, the global relationship quality score from the EAS, which ranges from 0 (worst relationship possible) to 100 (best relationship possible). Based on a previous RCT conducted by our team in 67 families of children with an NDD (CP),^24^ we assume the SD of the Global EAS will be 14.3 units, and that identifying a difference between the active (PACT) and waitlist control group of 5.0 units is clinically important. This is equivalent to a between-group difference of 0.35 SD. To achieve 80% power, 258 families (129 in each group) are required to provide outcome data (alpha=0.05). To allow for expected 11%–15% participant attrition (as experienced in our previous trials),^24^ we will recruit a total of 300 families into this RCT. Participant retention strategies will be guided by the consumer engagement panel and will include a quarterly study update. Sample size calculations were conducted using Stata statistical software V.14 (StataCorp, College Station, Texas).

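### The primary model leaves T1 as an unconstrained response and does not say which contrast tests T2; a baseline-adjusted T2 contrast would be more precise at no cost

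*Protocol article*

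**What the plan says.** In the Protocol article, section Statistical analysis of primary and secondary outcomes, the primary outcome goes into a mixed model that has time, with levels T1, T2 and T3, and group "included as the main effects, and a time-by-group interaction term". The only random term is for the child: "Child will be included as a random effect to account for the repeated measures from each participant". T1 is therefore one of the responses, and nothing sets the two arms' T1 means equal.

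After the sentence on secondary comparisons, the same section adds: "The value of the outcome variable at baseline will be included as a covariate when appropriate".

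The Hypotheses section fixes the primary time point as "immediately postintervention (T2; 12 weeks postbaseline, primary outcome".

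The Sample size section says: "The sample size calculation is based on the between-group difference for the primary outcome, the global relationship quality score from the EAS". It assumes an SD of 14.3 for the score and a difference of 5.0, and concludes that "258 families (129 in each group) are required to provide outcome data (alpha=0.05" for 80% power. It gives neither a baseline correlation nor an SD of change.

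**The concern.** The hypothesis concerns one time point, T2. The model yields more than one between-arm quantity that could be reported for T2, and the article does not choose between them. The T2-by-group coefficient compares change from T1; the group difference at T2 compares scores. Their standard errors differ unless rho is 0.5, and the sample-size section describes only the second.

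Neither makes efficient use of the T1 score, which is collected on every family before randomisation. Leaving the T1 means free makes the model estimate a baseline arm difference that randomisation sets to zero in expectation, and the T2 estimate pays for it. At stake is precision on the primary endpoint, and a choice between contrasts that should not be left open.

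**Working it through.** **Inputs.** From Sample size: SD 14.3, difference 5.0, 129 per arm, alpha 0.05. Sidedness is not stated; two-sided reproduces the figure. From the analysis section: responses at T1, T2 and T3, group, time, time-by-group, and a random effect for child. Assumed: rho, shown from 0.3 to 0.7; the same SD at T1 and T2; complete data on 129 per arm; normal approximation.

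**Step 1. Reproduce the plan's figure.** n per arm = 2 × (1.960 + 0.842)² × 14.3² / 5.0² = 128.4, rounded up to 129, so 258 in total. This matches exactly. The standard error is 14.3 × √(2/129) = 1.781, and power is Φ(5/1.781 − 1.960) = 80.2% (79.9% with the t distribution). The plan's figure is thus a two-sample comparison of scores at one time point, with no use of baseline.

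**Step 2. What the stated model offers.** Let D1 and D2 be the arm differences in mean score at T1 and T2.
- T2-by-group term: D2 − D1, the difference in mean change. SE = 1.781 × √(2(1 − rho)).
- Group plus T2-by-group: D2. SE = 1.781 whatever rho is.

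The generalised least squares variance of the stated random-intercept model, with three time points and 129 per arm, gives these same standard errors.

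**Step 3. Adjust for baseline.** With a common T1 mean in both arms, or with T1 as covariate, SE = 1.781 × √(1 − rho²). The generalised least squares variance of the common-mean model agrees.

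Example at rho = 0.4:
- Change contrast: SE = 1.781 × √1.2 = 1.951; power = Φ(5/1.951 − 1.960) = 72.7%.
- Adjusted contrast: SE = 1.781 × √0.84 = 1.632; power = Φ(5/1.632 − 1.960) = 86.5%.

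| rho (assumed) | T2-by-group: SE, power | T2 group difference: SE, power | Adjusted T2: SE, power | Total N for 80%: T2-by-group / adjusted |
|---|---|---|---|---|
| 0.3 | 2.107, 66.0% | 1.781, 80.2% | 1.699, 83.7% | 360 / 234 |
| 0.4 | 1.951, 72.7% | 1.781, 80.2% | 1.632, 86.5% | 310 / 216 |
| 0.5 | 1.781, 80.2% | 1.781, 80.2% | 1.542, 90.0% | 258 / 194 |
| 0.6 | 1.593, 88.1% | 1.781, 80.2% | 1.424, 93.9% | 206 / 166 |
| 0.7 | 1.379, 95.2% | 1.781, 80.2% | 1.272, 97.6% | 156 / 132 |

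**Step 4. Relative precision.** Variance of the change contrast over the adjusted one is 2(1 − rho)/(1 − rho²) = 2/(1 + rho), which is 1.54 at rho 0.3 and 1.18 at 0.7. Variance of the T2 group difference over the adjusted one is 1/(1 − rho²), which is 1/0.91 = 1.10 at rho 0.3 and 1/0.51 = 1.96 at 0.7. Both ratios exceed 1 for every rho strictly between 0 and 1.

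**Step 5. Does the baseline-covariate sentence repair this?** It follows the secondary comparisons and is conditional, so it does not clearly reach the primary model. If it did, T1 would be both response and covariate. A covariate that is constant within a family cancels out of that family's T2 − T1 difference. A simulation at rho 0.4 with 258 families gave a T2-by-group standard error of 1.95 both with and without T1 added, against 1.63 for proper adjustment.

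**The case against.** The strongest reply is that the article lists the interaction as a model term and never calls it the primary test. The hypothesis is stated at T2, the trial is sized on a between-group difference, and the model delivers that difference with 80.2% power at every rho. Naming the contrast is also something an article may leave to an analysis plan, which is not shown here. Randomisation keeps both contrasts unbiased, and leaving the T1 means free does not inflate the type I error. All of this stands. What remains is that the model itself is stated, and that a more precise one is available from data already planned.

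A reader might infer three stronger claims, none of which the document supports.
- **That the stated 80% power is wrong.** This would need the interaction to be the test and rho to be below 0.5. The document establishes neither. Above 0.5 the interaction has more than 80% power (99.3% at rho 0.8).
- **That the plan tests the three-level interaction jointly on 2 degrees of freedom.** No such test is specified, and the Hypotheses section already singles out T2.
- **That the inter-rater ICCs make rho below 0.5 likely.** The reported values run from 0.51 to 0.82, all above 0.5. They belong to the six individual scales, not to the global score that is the primary outcome. Getting from them to a rho below 0.5 needs a figure for true stability over 12 weeks, which the document does not give.

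**Conclusion.** The point holds as a free improvement to the primary analysis, not as an error that undermines the trial. The stated model leaves the T1 means free and does not tie the T2 hypothesis to one contrast. If the T2-by-group term is used, 258 families give 80% power only for rho of 0.5 or more, and the article should then state the rho it assumes. If the T2 group difference is used, the sample size is right but the baseline score is wasted.

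Baseline adjustment beats both. At 129 per arm and rho 0.3 to 0.7 its power is 83.7% to 97.6%, against 66.0% to 95.2% for the change contrast and 80.2% for the T2 difference. The power figures rest on assumed rho, equal SDs at T1 and T2 and complete data. Under the same conditions, the ranking holds for any rho strictly between 0 and 1.

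**What to change.** Name one primary test: the T2 between-group difference in the global EAS score, adjusted for T1. Estimate it in one of two ways:
- a longitudinal model with T1, T2 and T3 as responses and a common T1 mean in both arms, that is, no group effect at T1; or
- a model with T2 and T3 as responses and T1 EAS, interacting with time, as covariate.

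Do not use T1 as both response and covariate; reword the baseline-covariate sentence so that it is clear which models it covers. Report the T3 contrast from the same model as secondary. In Sample size, state that 258 is for an unadjusted T2 comparison and is conservative for this analysis.

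The cost is one paragraph of analysis wording and one sentence on sample size, settled before unblinding. It needs no new data, and the recruitment target of 300 stays as it is.

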## Methods and analysis

### Study design

This study is a hybrid type 1 RCT. A type 1 hybrid is focused on effectiveness while also exploring implementation. We will conduct an RCT of *PACT Online* with 300 families of children with NDD. This is a two-arm RCT in which families of a child (0–10 years) with a diagnosis of an NDD or assessed as having an increased likelihood of an NDD will be randomly assigned to *PACT Online* or CAU, with follow-up until 6 months postbaseline. All families will complete assessment at preintervention baseline (T1), immediate postintervention outcome (T2; 12 weeks postbaseline for CAU group) and follow-up (T3; 6 months postbaseline). As the *PACT Online* programme is secure and unable to be accessed by external parties during the study period, no between-group contamination is possible. Consolidated Standards of Reporting Trials guidelines will inform the conduct and reporting of this RCT (see figure 1).

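### Read as a random intercept, the child effect imposes one correlation on all three visits; if correlation decays, the T2 change test is conservative and the T3 change test is anticonservative

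*Protocol article*

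**What the plan says.** In the protocol article, the section on statistical analysis of primary and secondary outcomes plans a "mixed-model repeated-measures linear regression (multilevel modelling) with time (T1, T2, T3) and group" "included as the main effects, and a time-by-group interaction term". Baseline is thus one of three outcome levels, and the treatment terms are interactions with time. For the dependence between visits it says: "Child will be included as a random effect to account for the repeated measures from each participant". It names no random slope, residual covariance structure or robust standard error. It also does not say whether the effect is read as the interaction (difference in change from T1) or as the group difference at T2.

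The Hypotheses section places the primary comparison "immediately postintervention (T2; 12 weeks postbaseline, primary outcome" and predicts that "this effect will be sustained at follow-up (T3; 6 months post-baseline". The Study design section sets the visits: after baseline come "immediate postintervention outcome (T2; 12 weeks postbaseline for CAU group) and follow-up (T3; 6 months postbaseline". The Sample size section gives the only variance input: "we assume the SD of the Global EAS will be 14.3 units". No correlation between visits is given anywhere.

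**The concern.** With time as a three-level factor, a lone child random intercept with independent residuals is compound symmetry. It has one variance for all visits and one correlation for pairs 12, about 14 and about 26 weeks apart. A single pooled within-child variance then drives the standard errors of both change contrasts, T2-T1 and T3-T1.

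Repeated behavioural measures often correlate less as the gap grows, and T1 to T3 spans about twice the gap of T1 to T2. If that happens here, the pooled variance is too big for the short gap and too small for the long one. The trial would give up some power at its primary time point and test the sustained-effect prediction at more than the nominal 5%.

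**Working it through.** **Inputs from the protocol article.** SD 14.3, difference 5.0, power 80%, alpha 0.05 (taken as two-sided; the article does not say), 129 families per group, visits at 0, 12 and about 26 weeks.

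**Assumed.** The T1-T2 correlation r12 runs from 0.4 to 0.8. Under strong decay, correlation depends on elapsed time alone: r23 = r12^(14/12), r13 = r12^(26/12). Under mild decay, r23 = r12 and r13 = r12 − 0.10. Variances are equal and data complete unless stated.

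**The plan's own figure.** Per group, 2 × (1.96 + 0.8416)² × (14.3/5.0)² = 128.4, rounded up to 129. The stated 258 reproduces, and nothing below changes it.

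**Formulas.** With balanced complete data, the random-intercept model fits the mean of the three correlations, r̄.

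- Model SE of either change contrast: 14.3 × √(2(1 − r̄)) × √(2/129)
- True SE for visit k: the same with r1k in place of r̄
- Ratio, model to true: √((1 − r̄)/(1 − r1k))
- True alpha: 2 × (1 − Φ(1.96 × ratio))
- Power for 5 units: Φ((5 − 1.96 × model SE)/true SE)

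**Worked case, r12 = 0.6, strong decay.** r23 = 0.551, r13 = 0.331, r̄ = 0.494. Since 14.3 × √(2/129) = 1.7805:

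- model SE = 1.7805 × √1.012 = 1.79 at both visits
- true SE at T2 = 1.7805 × √0.8 = 1.59, ratio 1.125, true alpha 0.028
- true SE at T3 = 1.7805 × √1.338 = 2.06, ratio 0.870, true alpha 0.088
- power at T2: 0.825 as modelled, 0.881 with the correct SE

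| Decay | r12 / r23 / r13 | T2 ratio | T2 alpha | T2 power, modelled / correct | T3 ratio | T3 alpha |
|---|---|---|---|---|---|---|
| Mild | 0.4 / 0.4 / 0.3 | 1.03 | 0.044 | 0.709 / 0.727 | 0.95 | 0.062 |
| Mild | 0.6 / 0.6 / 0.5 | 1.04 | 0.041 | 0.864 / 0.881 | 0.93 | 0.068 |
| Mild | 0.8 / 0.8 / 0.7 | 1.08 | 0.034 | 0.990 / 0.993 | 0.88 | 0.084 |
| Strong | 0.4 / 0.34 / 0.14 | 1.09 | 0.033 | 0.669 / 0.727 | 0.91 | 0.076 |
| Strong | 0.5 / 0.45 / 0.22 | 1.11 | 0.030 | 0.740 / 0.802 | 0.89 | 0.082 |
| Strong | 0.6 / 0.55 / 0.33 | 1.13 | 0.028 | 0.825 / 0.881 | 0.87 | 0.088 |
| Strong | 0.8 / 0.77 / 0.62 | 1.16 | 0.023 | 0.985 / 0.993 | 0.84 | 0.100 |

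**Simulation.** 600 null trials of 258 families at 0.6 / 0.55 / 0.33 were fitted by REML with a random intercept.

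- T2 change: model SE 1.79, empirical SE 1.58, rejection 2.2%.
- T3 change: model SE 1.79, empirical SE 2.15, rejection 10.0%. The formula gives 8.8%; the Monte Carlo standard error is √(0.088 × 0.912/600) = 1.2 points, so the two agree.

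**Plain group difference at a visit.** Its SE is 14.3 × √(2/129) = 1.78 whatever the correlations. The simulation at T2 gave model SE 1.77, empirical SE 1.84 and rejection 5.5%.

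**Unequal variances.** At r12 = 0.6 with strong decay, several SD patterns between 12 and 16 kept both directions for the change contrasts: ratios 1.06 to 1.18 at T2 and 0.85 to 0.90 at T3. The plain group difference then loses its protection, with ratios of 0.93 to 1.07 at T2 and 0.92 to 1.14 at T3.

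**The case against.** **The structure is inferred.** The article never says intercept, only, or compound symmetry. A child effect can sit beside a freer residual covariance, and covariance details are commonly left to a statistical analysis plan, which is not shown here. This stands as a limit on certainty. It does not dispose of the point, because the article does state how repeated measures are handled, and the ordinary reading of that statement is a random intercept. If the analysis plan is freer, the two texts only need to be aligned.

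**The contrast is open.** The sample size is built on a between-group difference. If T2 is read as the group difference at that visit, the standard error is right under equal variances and complete data. This stands, and is why the contrast must be named. The stated model nevertheless makes the interaction the natural treatment term.

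**Decay is assumed.** This also stands. Rater noise in a coded 20-minute observation would lower all three correlations alike without creating decay. The table therefore includes mild decay, where T3 alpha is still 0.062 to 0.084. Exact equality of the three correlations is itself an assumption, and the article offers no support for it.

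**A stronger reading.** A reader might infer that the primary analysis is invalid or the trial underpowered because of this model. The documents do not support that. Under decay the T2 change test is conservative, and the stated sample size reproduces without reference to any correlation.

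**Conclusion.** The point holds in conditional form. If the child effect is a lone random intercept, effects are read as change from T1, and correlation decays with time, then the two change contrasts have standard errors that err in opposite directions.

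- **T2 (primary):** SE too large by 3% to 16%, true alpha 0.044 to 0.023, power loss from under 1 to about 6 points. This is an avoidable inefficiency and no threat to validity.
- **T3 (sustained effect):** SE too small by 5% to 16%, true alpha about 0.06 to 0.10. This is the main reason to act.

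These ranges rest on assumed correlations, equal variances and complete data. With the 11% to 15% attrition that the Sample size section expects, likelihood estimates under missing at random also depend on the fitted covariance. That effect is not quantified here. The change is worth making, chiefly for T3.

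**What to change.** In the section on statistical analysis of primary and secondary outcomes:

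1. Replace the child random effect with an unstructured 3×3 residual covariance over T1, T2 and T3, fitted by REML with Kenward-Roger degrees of freedom.
2. State the fallback if the model does not converge: a heterogeneous structure with robust standard errors.
3. Name the exact T2 and T3 contrasts, as difference in change from T1 or as group difference at the visit.
4. Do the same for secondary outcomes analysed over all three visits. Where baseline is a covariate and only T2 and T3 are outcomes, there is a single correlation, so the equal-correlation problem does not arise; unequal variances should still be allowed.

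The covariance then has six parameters instead of two, which is little for 300 recruited families or the 258 expected to give outcome data. Robust standard errors alone would mend the standard errors but not the covariance's role in handling dropout, so they belong in the fallback. The cost is a short change of text and code plus a small convergence risk, and it should be made before outcome data are seen by group.
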